|                             |                                                                                                                                                                                                                                                  |                                                         |          |
|-----------------------------|--------------------------------------------------------------------------------------------------------------------------------------------------------------------------------------------------------------------------------------------------|---------------------------------------------------------|----------|
|                             |                                                                                                                                                                                                                                                  | according to Australian Bureau of Statistic guidelines. |          |
| Current employment status   | Self- reported in response to “Which of the following best describes your current employment status?”
Options:
1=Working full time
2=Working part time or casual
3=Sick leave
4=Not employed
5=Retired
6=Other: (open text) | Reported as a number and %                              | Baseline |
| Current relationship status | Self-reported in response to “Which of the following best describes your relationship status?”
Options:
1=Single
2=In a relationship/married
3=Other: (open text)                                                                    | Reported as a number and %                              | Baseline |

| Baseline medical history               | Description                                                                                                                                                                                                          | Data                                                                                                                                           | Time-point measured |
|----------------------------------------|----------------------------------------------------------------------------------------------------------------------------------------------------------------------------------------------------------------------|------------------------------------------------------------------------------------------------------------------------------------------------|---------------------|
| Birth History                          | Self-reported in response to:

1. How many times have you given birth? 0 – 1, 2,3
2. How many of your births were vaginal delivery?                                                                         | Reported as a number and %
Mean & SD                                                                                                        | Baseline            |
| Hormone status                         | Hormone status post cancer treatment will be self-reported by asking the participant to select from the list:
1=Pre-menopausal
2=Peri-menopausal
3=Post-menopausal
4=Surgical menopause
5= Don't know | Reported as a number and %                                                                                                                     | Baseline            |
| Pelvic floor problems                  | Participants will be asked to indicate if they experienced bladder or bowel incontinence prior to cancer treatment:
Options:
1. Urinary Incontinence
2. Faecal Incontinence                                 | Reported as a number and %                                                                                                                     | Baseline            |
| Co-morbidity                           | Reported using the Self-Administered Comorbidity Questionnaire [49]                                                                                                                                                  | Reported as number and %
OR
comorbidities per participant will be summed and comorbidities for the cohort will be reported as Mean (SD). | Baseline            |
| Cancer specific medical history |                                                                                                                                                                                                                      |                                                                                                                                                |                     |
| Stage of cancer when diagnosed         | Self-reported by selecting from:
1. Stage I
2. Stage IIA
3. Stage IIB
4. Stage IIC
5. Stage II unsure which level
6. Stage IIIA
7. Stage IIIB                                                   | Reported as number and %                                                                                                                       | Baseline            |

|                                      |                                                                                                                                                                                                                                                                                                                        |                                        |          |
|--------------------------------------|------------------------------------------------------------------------------------------------------------------------------------------------------------------------------------------------------------------------------------------------------------------------------------------------------------------------|----------------------------------------|----------|
|                                      | 8. Stage IIIC
9. Stage III unsure which level
10. Recurrent cancer                                                                                                                                                                                                                                               |                                        |          |
| Cancer location                      | Self-reported by selecting from:
1. Uterus
2. Cervix
3. Ovary
4. Fallopian tube
5. Primary peritoneal                                                                                                                                                                                                   | Reported as number and %               | Baseline |
| Time since last treatment for cancer | Self-reported in response to “What date did your last cancer treatment end?” Response converted into months.                                                                                                                                                                                                           | Reported as mean (SD) or median (IQR). | Baseline |
| Past cancer treatment details        | Self-reported by selecting from:
1. Surgery
2. Pre-operative chemotherapy
3. Pre-operative radiotherapy
4. Post-operative chemotherapy
5. Post-operative radiotherapy
6. other

If women had radiotherapy they will be asked if they had
i. External beam radiotherapy
ii. Brachytherapy | Reported as number and %               | Baseline |
| Vaginal dilator therapy              | Participants will be asked if they have done vaginal dilator therapy:
1=Yes, I am currently doing
2=Yes, but I have stopped
3=No, I have not done this                                                                                                                                                        | Reported as number and %               | Baseline |

| Process and other measures                      | Description                                                                                                                                                                                                                                                                                                                                                                                                                                           | Data                                                       | Time-points measured                |
|-------------------------------------------------|-------------------------------------------------------------------------------------------------------------------------------------------------------------------------------------------------------------------------------------------------------------------------------------------------------------------------------------------------------------------------------------------------------------------------------------------------------|------------------------------------------------------------|-------------------------------------|
| Clinical measures                               | Data relating to PFMT and PFM function will be collected by the femfit® biofeedback device. This will include the magnitude, duration and timing of pressure changes, reflecting the muscle contraction strength, endurance and repetitions.
This data will automatically be uploaded and stored on a secure server via the femfit® smartphone app. Data will be exported by the treating study physiotherapist and provided to the research team. | Pressure manometry will be reported in mmHg and seconds    | At first and last treatment session |
| Exercise adherence                              | Adherence to the prescribed home exercise program will be collected within the femfit® app exercise diary.                                                                                                                                                                                                                                                                                                                                            | Reported as a number and %                                 | 17 weeks (intervention group only)  |
| Attendance at physiotherapy video-consultations | The number of physiotherapy consultations completed by each participant will be recorded by the physiotherapist in the treatment notes.                                                                                                                                                                                                                                                                                                               | Reported as a number and % of the total scheduled sessions | 17 weeks (intervention group only)  |
| Treatment satisfaction                          | Self-reported in response to “How satisfied are you with the intervention that you received in this study?”

Responses will be captured on a 7-point Likert scale ranging from                                                                                                                                                                                                                                                                  | Reported as a number and %..                               | 17 and 52 weeks                     |

|                                               |                                                                                                                                                                                                                                                                                                                                                                                                                                          |                                                                                                          |                        |
|-----------------------------------------------|------------------------------------------------------------------------------------------------------------------------------------------------------------------------------------------------------------------------------------------------------------------------------------------------------------------------------------------------------------------------------------------------------------------------------------------|----------------------------------------------------------------------------------------------------------|------------------------|
|                                               | 1=extremely unsatisfied to 7=extremely satisfied                                                                                                                                                                                                                                                                                                                                                                                         |                                                                                                          |                        |
| Health problems                               | Change in health status will be defined as any change from the participant's baseline (pre-treatment) condition, other than improvement. Information will be collected within the follow-up questionnaires via a custom-developed table.
All changes to health status data will be aggregated.                                                                                                                                        | Types/categories of health changes will be reported. Reported as number and %                            | 17 and 52 weeks        |
| Cancer treatment since commencing this study  | Participants will be asked if they have had any cancer treatment since completing their last study questionnaire. If yes, participants will be asked to select which apply
1. Chemotherapy
2. Radiotherapy
3. Surgery
4. Other (open text)
5. No, I have not had any                                                                                                                                                      | Reported as number and %                                                                                 | 17, 52 weeks           |
| Additional cancer treatment                   | Participants will be asked if they have had any targeted therapy or immunotherapy in addition to chemotherapy, radiotherapy and surgery. If yes, participants will be asked to indicate whether they are currently on this/these treatment(s) or to provide stop date.                                                                                                                                                                   | Reported as a number and %                                                                               | Baseline, 17, 52 weeks |
| Medications relevant to pelvic floor function | Self-reported via a custom-developed table listing common medications which can affect bladder, bowel, sexual function. Participants will be asked to select, from the list, which medications they have taken in the past week.                                                                                                                                                                                                         | Whole numbers/ counts from 0.
Reported as a number and %                                              | Baseline, 17, 52 weeks |
| Current exercise levels: pelvic floor muscle  | Participants will be asked if they currently do pelvic floor muscle exercises and to select how often from options
0= Not currently doing
1= Less than 1 time a month
2= At least 1 time a month
3=At least 1 time a week
4= At least 3 times a week
5= At least 3 times a day                                                                                                                                         | Reported as number and %                                                                                 | Baseline, 17, 52 weeks |
| Adverse Events                                | Adverse events (AE) will be defined as any change from the participant's baseline (pre-treatment) condition, other than improvement. Information about AEs will be collected in two ways:
i) self-reported within the follow-up questionnaires via a custom-developed table and/or
ii) reported directly to the research team as per section 7. 'Adverse event reporting' within this protocol.
All AE data will be aggregated. | Type of adverse events and proportions of participants experiencing each adverse event will be reported. | 17 and 52 weeks        |

| Health Economic Data                               | Description                                                                                                                                                                                                                                                                                                                                                                                            | Data                                                      | Time-points measured               |
|----------------------------------------------------|--------------------------------------------------------------------------------------------------------------------------------------------------------------------------------------------------------------------------------------------------------------------------------------------------------------------------------------------------------------------------------------------------------|-----------------------------------------------------------|------------------------------------|
| Cost of physiotherapist's time                     | The cost of physiotherapy services provided to each participant will be calculated by the research team.                                                                                                                                                                                                                                                                                               | Reported as the dollar cost per participant (mean and SD) | 17 weeks (Intervention group only) |
| Cost of resources                                  | The cost of intervention resources provided to each intervention group participant will be calculated by the research team. Resources include the biofeedback devices and package of participant resources                                                                                                                                                                                             | Reported as the dollar cost per participant (mean and SD) | 17 weeks (Intervention group only) |
| Cost of pads for bladder leakage                   | To estimate costs of pad use for incontinence we will collect details of
- disposable pads including brand name, cost and average number used via Table 1 of the Dowell Bryant Incontinence Cost Patients Index (DBICI)[50].
- reusable incontinence underwear including brand and cost.
This information will be collected from participants using retrospective recall over the past month. | Reported as the dollar cost per participant (mean and SD) | Baseline, 17 and 52 weeks          |
| Laundry associated with incontinence               | Collected from participants using a modified version of Table 3 of the DBICI [50].
This information will be used to calculate laundry costs related to incontinence.                                                                                                                                                                                                                                | Reported as the dollar cost per participant (mean and SD) | Baseline, 17 and 52 weeks          |
| Health service use related to urinary incontinence | Health professional appointments, surgeries, investigations, and medications relating to urinary incontinence will be collected from participants using Section 2 of the DBICI [50].
This information will be used to calculate treatment expenditure.                                                                                                                                              | Reported as the dollar cost per participant (mean and SD) | Baseline, 17 and 52 weeks          |
| Work productivity                                  | Information about paid employment or self-employed, leave and job performance will be collected from participants via a custom-built questionnaire                                                                                                                                                                                                                                                     | Reported as mean (SD) and number and % where appropriate  | Baseline, 17 and 52 weeks          |

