| Secondary Outcomes                                                                                                 |                                                                                                                                                                                                                                                                                                                                                                                 |                                                                                                                                                                                                                                                                          |                           |                                                                                                                          |
| International Consultation on Incontinence Questionnaire Lower Urinary Tract Symptoms Quality of Life (ICIQ-LUTSqol) [42] | 
A 20-item self-reported questionnaire capturing the impact of any type of urinary incontinence on quality of life.
 
Items are summed to create one overall score.
 
Domain-specific scores within seven domains (role limitation, physical limitations, personal relationships, emotions, sleep/energy, severity measures) will also be calculated.
           | 
Overall score ranges from 19-76. Higher scores indicating increased impact on quality of life.
 
The domain-specific scores will be calculated using a specific scoring method developed by the ICIQ group. Domain scores range from 0 (best) to 100 (worse)
 | Baseline, 17 and 52 weeks | Constrained longitudinal data analysis across all time points, accounting for stratification factor and physiotherapist. |

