|------------------------------------------------------------------------|-------------------------------------------------------------------------------------------------------------------------------------------------------------------------------------------------------------------------------------------------------------------------------------------------------------------------------------------------------------------------------------------------------------------------------------------------------------------------------------------------------------------------------------------------------------------|------------------------------------------------------------------------------------------------------------------------------------------------------------------------------------------------------------------------------------------------------------------|---------------------------|---------------------------------------------------------------------------------------------------------------------------|
| EQ-5D-5L [44, 45]                                                      | 
Health-related quality of life is self-reported via
 
 
- five dimensions: mobility, self-care, usual activities, pain/discomfort and anxiety/depression. Each dimension has 5 levels: no problems, slight problems, moderate problems, severe problems and extreme problems (descriptive component) and
 
- one additional self-rated health question scored on a visual analogue scale ranging from “the best health you can imagine” to “the worst health you can imagine” (evaluation component).
 
 | 
Ranges from -0.285 to 1.00; a negative value represents a health state that is worse than death.
 
An index score will be calculated as 1 minus the total utility captured in the EQ-5D-5L
 
The visual analogue scale score ranges from 0 -100
 | Baseline, 17 and 52 weeks | Constrained longitudinal data analysis across all time points, accounting for stratification factor and physiotherapist.  |

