### 12.2 Statistical Analysis Plan

All analyses will be described *a priori* in a detailed Statistical Analysis Plan and published while biostatisticians are blinded to treatment allocation. Demographic and baseline characteristics of participants will be summarised as appropriate (means and standard deviations for continuous variables that appear to be distributed approximately symmetrically, medians and interquartile ranges for other continuous variables, counts and percentages for categorical variables). Main comparative analyses between groups will be performed using intention-to-treat. Constrained longitudinal data analysis will be used to analyse continuous outcomes, including the primary outcome. The response will consist of all continuous outcomes (baseline, 17 weeks and 52 weeks) and the model will include factors representing treatment group, time (categorical), and a group-by-time interaction, with the restriction of a common baseline mean across treatment groups. Models will include the stratification

variable (radiotherapy) and random effects for physiotherapist (intervention arm only). The mean change in urinary incontinence (primary outcome) and other continuous outcomes (ICIQ-LUTSqol, PFBQ, EQ-5D-5L, UTAUT-II domains 1-9, METminutes (walking, moderate-intensity activities, vigorous-intensity activities) from baseline to each follow-up time-point between the two intervention groups will be obtained. The primary hypothesis will be evaluated by obtaining the estimated differences between the two intervention arms in mean change in urinary incontinence score from baseline to 17-weeks post-commencement of treatment (primary time point), two-sided 95% confidence intervals and p-values. These models provide valid inference in the presence of missing data if the data are missing at random. Standard diagnostic plots will be used to check model assumptions. Treatment effects at 52 weeks post-randomisation (secondary time point) will be estimated to assess maintenance of treatment effects for all outcomes except UTAUT-II domains 1-9 for which only 17-week follow-up data will be collected.

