The binary secondary outcomes (PGIC and physical activity category) will be compared between groups separately using logistic regression, adjusting for the stratifying variable of radiotherapy, and fit using generalized estimating equations to account for clustering, with results reported as risk ratios and risk differences. Poisson regression models fitted using generalized estimating equations will be used for secondary count outcomes (number of leakage episodes overall and by severity and provocation, number of continence pads used).

The economic evaluation will have a societal perspective and will assess both the cost of the intervention at 17 weeks and the cost-effectiveness and cost-utility of the intervention group *versus* the control group at 52-weeks. Quality-adjusted life years (QALYs) gained [56] for the intervention compared to control at 52 weeks will be assessed. QALYs will be calculated based on utility scores using the EQ-5D-5L [44, 45] at baseline and 52 weeks. QALYs will also be calculated using the ICIQ-LUTSqol [42], a condition specific quality of life measure, at baseline and 52 weeks. Analysis will be combined with the primary clinical outcome measure to establish the incremental cost-effectiveness ratio of the intervention. The difference in participant resource use related to incontinence (e.g. pad use, medication use, health service use) and productivity lost between baseline and 52 weeks will be compared for intervention and control groups. The association between utility gains on the EQ-5D-5L and productivity will be compared between the intervention and control groups. The 52-week economic evaluation will be reported separate from the main trial.

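### The EQ-5D-5L index is defined as 1 minus the utility, which contradicts the range stated beside it and reverses the direction of this secondary outcome

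*Protocol*

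**What the plan says.** Protocol section 4.6 lists the EQ-5D-5L as a secondary outcome, measured at baseline, 17 and 52 weeks. Its Scale cell makes two statements in succession about the index. The first is the range: "Ranges from -0.285 to 1.00; a negative value represents a health state that is worse than death". The second is the scoring rule: "An index score will be calculated as 1 minus the total utility captured in the EQ-5D-5L".

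Section 12.2 puts the measure among the "other continuous outcomes (ICIQ-LUTSqol, PFBQ, EQ-5D-5L, UTAUT-II domains 1-9", analysed by constrained longitudinal data analysis with between-group differences in mean change. For the economic evaluation the same section says: "QALYs will be calculated based on utility scores using the EQ-5D-5L [44, 45] at baseline and 52 weeks".

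**The concern.** The range sentence fixes the direction of the scale. If negative values are worse than death and the maximum is 1.00, then 1.00 is the best state and higher is better. The scoring sentence subtracts that quantity from 1, which turns the scale over. The two sentences describe different variables, so an analyst cannot satisfy both.

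At stake is the sign of a secondary treatment effect. The scoring sentence is the only formula for the index in the protocol. The row also does not say outright what a higher index means, whereas the rows for the ICIQ-UI SF, ICIQ-LUTSqol, PFBQ and UTAUT-II do. Someone who programs from the formula and reports the result as an EQ-5D-5L index would present better health in the intervention arm as worse health, or the reverse.

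**Working it through.** **Inputs.** All are from the EQ-5D-5L row of Protocol section 4.6: lower end of the range -0.285; upper end 1.00; negative means worse than death; rule as written, index = 1 - u, where u is the utility.

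**Step 1: apply the rule as written to the stated range.**
- Best state, u = 1.00: index = 1 - 1.00 = 0.
- An intermediate value for illustration, u = 0.80: index = 1 - 0.80 = 0.20.
- Worst state, u = -0.285: index = 1 - (-0.285) = 1.285.

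The index runs from 0 to 1.285 with the best state lowest. It has no negative values, so the stated range of -0.285 to 1.00 is not reproduced.

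**Step 2: try the nearest alternative reading.** Suppose the intended rule is index = 1 - D, where D is the total utility decrement from full health. For the stated range, D must run from 1 - 1.00 = 0 to 1 - (-0.285) = 1.285.
- D = 0: index = 1 - 0 = 1.00.
- D = 1.285: index = 1 - 1.285 = -0.285.

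This reproduces the stated range exactly, with higher being better. Under this reading the index is simply the utility.

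**Step 3: effect on the secondary outcome.** For a change from u0 to u1, the index as written changes by (1 - u1) - (1 - u0) = -(u1 - u0).
- Illustration, utility 0.70 to 0.80: (1 - 0.80) - (1 - 0.70) = 0.20 - 0.30 = -0.10 instead of +0.10.
- Illustration, a between-group gain of 0.05 becomes -0.05.

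Because 1 - u is a linear transformation with slope -1, the fitted linear model gives the same standard error and p-value, and the confidence interval is mirrored about zero. Only direction is affected, so nothing in the size of the estimate or its precision would give the error away. The 0.70, 0.80 and 0.05 are illustrations, not protocol figures.

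**Step 4: does it reach the QALYs?** Assume the area under the curve over one year from the two time points that section 12.2 names, (baseline + week 52)/2.
- From the utility, 0.70 and 0.80: (0.70 + 0.80)/2 = 0.75.
- From the index as written: (0.30 + 0.20)/2 = 0.25, which is 1 - 0.75.
- A full year at u = 1.00 gives 1 from the utility and 0 from the index as written.

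The second set of figures arises only if the section 4.6 index is substituted for the utility. Section 12.2 names utility scores, so on its own wording the QALY comes from the first set.

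**The case against.** The best defence is that this is a missing word that the cell itself gives away. The range and the meaning of negative values stand immediately before the rule, and only one reading fits them. An analyst who applied the formula literally could obtain values above 1.00, outside the protocol's own range, and would probably notice. Much of this stands: the sentence is most likely a slip, and a reversed analysis is a risk, not a forecast. It does not remove the point. Index values above 1.00 arise only for utilities below zero. If no participant reports a state worse than death, every value of 1 - u lies between 0 and 1, inside the stated range, and no range check would fail.

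Two stronger readings are tempting, and the protocol supports neither.

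A reader might infer that the incremental QALY, and with it the cost-utility conclusion, changes sign. Section 12.2 bases the EQ-5D-5L QALYs on utility scores and does not refer to the section 4.6 index. The reversal follows only if one is substituted for the other. The cost-effectiveness analysis is in any case conditional on clinical effectiveness at 17 weeks (sections 3.2 and 9.3), and section 12.2 reports the 52-week economic evaluation separately from the main trial.

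A reader might also infer that a second QALY analysis is invalid, because section 12.2 adds "QALYs will also be calculated using the ICIQ-LUTSqol [42], a condition specific quality of life measure, at baseline and 52 weeks" while the scores defined for that instrument in section 4.6 are a total ("Overall score ranges from 19-76. Higher scores indicating increased impact on quality of life") and domain scores from 0 to 100, neither of which is a utility. But the protocol nowhere says that these raw scores will serve as QALY weights. A conversion may be specified in the statistical analysis plan or a health-economic plan, neither of which is at hand. The most that can be said is that the protocol states no conversion to utilities. That is a note, not an error, and it forms no part of this point.

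**Conclusion.** The point holds for the EQ-5D-5L index in section 4.6. As written, the rule gives a scale of 0 to 1.285 with the best state lowest, against a stated scale of -0.285 to 1.00 with the best state highest. If followed, it would reverse the sign of every between-group difference on this index at 17 and 52 weeks and leave magnitude and precision unchanged.

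The contradiction rests only on the two sentences in that cell and needs no outside source. That the author meant the decrement is an inference, though a strong one, because that reading returns the stated range exactly. The consequence assumes that the formula is programmed literally and the result reported as if higher were better.

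The reach is limited: one secondary outcome directly, and the QALYs only if the index as now worded replaces the utility scores. The primary outcome, its model and the sample size are not touched. It should be corrected before the analysis is programmed, but it does not threaten the trial's main conclusion.

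**What to change.** In section 4.6, replace the scoring sentence with: index = 1 minus the sum of the value-set utility decrements, i.e. the utility itself; range -0.285 to 1.00; higher is better. In section 12.2, state that this same index is what is meant wherever EQ-5D-5L utility scores are mentioned, so that the secondary outcome and the QALYs use one variable with one direction. The statistical analysis plan should carry the same definition.

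The cost is one replaced sentence and one short cross-reference. Questionnaires, data already collected, the analysis model and the sample size do not change.
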